## Abstract

**Abstract:**

**Introduction:**

The incidence of gestational diabetes mellitus (GDM) in Australia has tripled in the last 20 years. Consequently, over 40 000 pregnancies are now diagnosed as ‘higher risk’ each year. This has increased antenatal surveillance and obstetric intervention, often in the form of delivery earlier than 39 weeks gestation. The StUdy of Gestational diabetes And Risk using Electronic Data (SUGARED) project aims to use large population-based and routinely collected linked health data to (1) personalise risk prediction of adverse pregnancy outcomes for women undergoing glucose tolerance testing, (2) guide optimal birth timing for women with diet-controlled GDM and (3) examine variation in GDM management and pregnancy outcomes in New South Wales (NSW), Australia.

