### Explanatory variables

Individual explanatory variables will include as follows:

Demographic and socioeconomic factors:Maternal age.Country of birth.Aboriginality.Residence remoteness, calculated using Statistical Area 2 of residence (SA2), the Australian Bureau of Statistics (ABS) remoteness classification for Statistical Area 1 and the population-weighted correspondence to SA2.Area-level socio-economic status (using the ABS Socio-Economic Indices for Areas classification for SA2).Maternal risk factors:Maternal height, weight and BMI.Previous birth outcomes.Parity.Smoking in pregnancy.History of endocrine, metabolic and gynaecological conditions.Chronic conditions and previous surgery.Pregnancy risk factors:Plurality.Gestational hypertension and pre-eclampsia.Assisted reproductive technology.Antenatally identified foetal growth restriction and macrosomia.Antenatal electrolytes and results of liver function tests, full blood count coagulation studies and urine tests.Antenatal medical treatment of GDM (insulin, oral hypoglycaemic medication).Health service use:Birth hospital.Antenatal care information.Model of care.Antenatal ED and hospital admissions.Labour and birth characteristics:Labour onset, induction and augmentation of labour.Labour interventions.Mode of birth.Pain relief.Gestational age.

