**Figure 3 F3:**
[figure not shown]
Derivation and validation cohorts for each of the eight folds.

Using the derivation cohort, univariate repeated measures logistic regression modelling will assess the relationship between the primary composite outcome (any of the following: large for gestational age, stillbirth, neonatal death, shoulder dystocia, bone fracture, arm/hand palsy related to birth injury, gestational hypertension or pre-eclampsia) and explanatory variables. Repeated measures logistic regression will take into account the non-independence of two or more pregnancies to the same woman during the study period. Two-way interactions (eg, BMI and hyperglycaemia) will be examined, and the collective and individual effect on the multivariate model assessed. Multivariable repeated measures logistic regression will estimate adjusted ORs and their 95% CIs.

Using the validation cohort, agreement between the predicted and observed probabilities of the primary composite outcome will be assessed by Hosmer-Lemeshow goodness of fit testing.^25^ Ability of the prediction model to differentiate high-risk and low-risk women will be assessed using area under the receiver operating characteristics curve.^26^ The sensitivity, specificity, negative and positive predictive values will be calculated for each validation cohort.

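### Aim 1 lists gestational hypertension and pre-eclampsia both as components of the primary composite and as explanatory variables; the same list also holds labour and birth variables that are unknown when the prediction is to be used

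*Protocol article*

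**What the plan says.** **The outcome.** The section on risk prediction models (aim 1) defines "the primary composite outcome (any of the following: large for gestational age, stillbirth, neonatal death, shoulder dystocia, bone fracture", and the definition ends "arm/hand palsy related to birth injury, gestational hypertension or pre-eclampsia) and explanatory variables". The rule is any-of, so one component makes a woman a case. The sentence names no subset of the explanatory variables.

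**The predictors.** The Explanatory variables section is the only such list in the article. It opens with "Individual explanatory variables will include as follows" and is not divided by aim. It contains "Pregnancy risk factors:Plurality.Gestational hypertension and pre-eclampsia.Assisted reproductive technology" and, further down, "Labour and birth characteristics:Labour onset, induction and augmentation of labour.Labour interventions.Mode of birth.Pain relief.Gestational age".

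**The point of use.** The Abstract describes the aim as to "personalise risk prediction of adverse pregnancy outcomes for women undergoing glucose tolerance testing". The Introduction says that aim 1 results should help obstetricians to target surveillance and intervention. The Ethics and dissemination section foresees possible risk tools for consultations with women who are still pregnant. All three uses come before birth.

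**The evaluation.** In each validation cohort the plan assesses calibration by a Hosmer-Lemeshow test and discrimination by AUC, with sensitivity, specificity and predictive values. The multivariable model is to give adjusted odds ratios with 95% confidence intervals.

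**The concern.** There are two separate faults.

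The first is circularity, and it concerns only the two hypertensive conditions. If they enter the model as predictors, part of the outcome is on both sides of the equation. The model then looks better than it is, and its high-risk group partly consists of women who already have the outcome. Cross-validation offers no protection, because the link is definitional and holds in every fold.

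The second is timing. Labour onset, induction, labour interventions, mode of birth, pain relief and, judging by its heading, gestational age at birth are not composite components. They are known only at or near birth, so a model that uses them cannot be applied when an antenatal risk estimate is wanted.

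Aim 1 may feed a clinical risk tool, so overstated discrimination could reach its users.

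**Working it through.** **Step 1: compare the two texts.**

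| Variable | In the aim 1 composite | In the explanatory list | Known at an antenatal consultation |
|---|---|---|---|
| Gestational hypertension, pre-eclampsia | Yes | Yes, as pregnancy risk factors | Only if already present |
| Labour onset, induction, labour interventions, mode of birth, pain relief | No | Yes, as labour and birth characteristics | No |
| Gestational age (read as at birth, from its heading) | No | Yes, same heading | No |

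**Step 2: what follows without any assumed rate.** Let h = 1 if the woman has either hypertensive condition and y = 1 if she has the composite. The any-of rule gives P(y = 1 | h = 1) = 1, so the cell h = 1, y = 0 is empty. Women with h = 0 occur in both outcome groups, so this is quasi-complete separation. Women with h = 1 contribute only terms log p to the log-likelihood. Each of these rises without limit point as the coefficient of h grows, so no finite maximum exists and the planned odds ratio and interval for h cannot be estimated. Taken alone, h has specificity 1, positive predictive value 1 and sensitivity s, where s is the share of composite cases with a hypertensive condition. This assumes that the predictor and the component are ascertained in the same way.

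**Step 3: effect on the AUC.** The AUC is the probability that a random case scores above a random non-case. A share s of cases has h = 1 and no non-case does, so these cases always rank on top. For the remaining share, let A be the AUC of the other predictors. Then

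AUC = s + (1 − s) × A.

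With h alone, A = 0.5 and the AUC is 0.5 + s/2.

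| s (assumed) | h alone | With A = 0.65 (assumed) |
|---|---|---|
| 0.1 | 0.55 | 0.685 |
| 0.2 | 0.60 | 0.720 |
| 0.3 | 0.65 | 0.755 |
| 0.4 | 0.70 | 0.790 |
| 0.5 | 0.75 | 0.825 |

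**Step 4: simulation.** The article gives no event rate or AUC for aim 1, so there is no stated figure to reproduce. Only n = 70 000 comes from the article (more than 70 000 GDM pregnancies). All rates are assumed, as is one genuine predictor with a log-odds slope of 0.5 per standard deviation for both kinds of event.

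| Hypertensive | Other components | Composite | s | AUC without h | AUC with h |
|---|---|---|---|---|---|
| 5% | 10% | 14.3% | 0.346 | 0.640 | 0.760 |
| 5% | 15% | 19.2% | 0.262 | 0.637 | 0.727 |
| 5% | 20% | 23.8% | 0.210 | 0.640 | 0.711 |
| 8% | 10% | 17.0% | 0.469 | 0.644 | 0.807 |
| 8% | 15% | 21.6% | 0.376 | 0.642 | 0.772 |
| 8% | 20% | 26.2% | 0.308 | 0.642 | 0.747 |
| 12% | 10% | 20.5% | 0.576 | 0.643 | 0.847 |
| 12% | 15% | 25.0% | 0.482 | 0.639 | 0.807 |
| 12% | 20% | 29.2% | 0.408 | 0.648 | 0.785 |

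The cell h = 1, y = 0 was 0 in all nine settings. A maximum-likelihood logistic fit in the last setting failed with a singular matrix. The formula agrees with the simulation: in the third row, 0.210 + 0.790 × 0.640 = 0.716 against 0.711. The small gap arises because A applies to the non-hypertensive cases, whose AUC is slightly below that for the whole composite.

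**The case against.** The best defence is that the Explanatory variables section is a menu for the whole project. It precedes all three analysis plans, and a variable's role changes with the question: the aim 3 section takes induction as exposure and caesarean section as outcome. Birth hospital and the labour variables have clear uses in aims 2 and 3. The authors may well intend a subset for aim 1, and a condensed article may leave per-model candidate lists to an analysis plan. A non-finite odds ratio would also show at the planned univariate step.

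Much of this stands. It would be too strong to say that the authors will fit every listed variable in aim 1, or that the tool is therefore unusable in antenatal clinic. The absence of a detailed candidate list is not in itself the fault. The defence does not remove the conflict, however. The aim 1 text points to explanatory variables, the only list under that name contains two components of the outcome, and nothing takes them out. That is stated on the page. An alert analyst would probably notice the failed fit, but the protocol should not depend on that.

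A reader might also infer that treatment of GDM and antenatally identified macrosomia or growth restriction must be deleted, and that prediction must be fixed at the glucose tolerance test. The article does not support this. Only the Abstract points to the test. The aim 1 population is women with diagnosed GDM, and the Ethics and dissemination section describes dynamic tools for consultations with such women, when treatment and growth findings may already be known.

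**Conclusion.** The point holds in two parts.

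1. The hypertensive conditions are both outcome component and listed predictor. The empty cell, the non-finite odds ratio and the upward direction of the bias follow from the definition, given the same ascertainment in both roles. The size does not: an AUC rise from 0.64–0.65 to 0.71–0.85 rests on assumed event rates and one assumed modest predictor, and should be read as an illustration.
2. The labour and birth characteristics come too late for the stated antenatal use.

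A reader might extend the circularity to mode of birth, labour onset or gestational age, but these are not composite components and their fault is timing only. Nor is the separation complete, since women without a hypertensive condition fall in both outcome groups. The correction should be made before the aim 1 models are fitted, because the model as written has a predictor whose effect cannot be estimated and performance measures that would mislead.

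**What to change.** In the aim 1 section:

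- State an antenatal prediction time, and limit candidate predictors to information available by then.
- Exclude gestational hypertension and pre-eclampsia of the index pregnancy from the candidates. Alternatively, if they are wanted as predictors, take them out of the composite.
- Exclude all labour and birth characteristics, including gestational age at birth.
- Let GDM medication and antenatally identified growth findings stay if they are known by the stated time.
- Say that the general list of explanatory variables serves all three aims and that each aim uses a subset.

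The change is one of wording and needs no new data. The price is a lower reported AUC. If the hypertensive conditions leave the composite instead, there will also be fewer outcome events and a narrower outcome to interpret.

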## Methods and analysis

### Study design and population

This is a retrospective cohort study using linked routinely collected health data. All women who gave birth in NSW from January 2016 to December 2020 are included. The cohort will comprise approximately 475 000 pregnancies, with >70 000 diagnosed with GDM.

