### Analysis plan: risk prediction models (aim 1)

A K-fold approach will be used to derive and validate risk prediction models identifying groups of women with GDM who are at higher or lower risk of adverse outcomes. The study population, comprising all women in the cohort who have been identified as having GDM, will be randomly divided into roughly equal subgroups balancing prediction error and computational time. In each fold, one subgroup will be a validation cohort, and the other subgroups will be combined as the derivation cohort. Figure 3 provides an illustration of the k-fold approach using an 8-fold as an exemplar of the methodology, where the whole population gets randomly assigned to eight roughly equal groups. Once assigned, individuals remain in their allocated group. A ‘fold’ refers to a round of analysis where the remaining groups are combined to generate the risk prediction model while the validation cohort is then used to validate it. In an eightfold, these analyses are run eight times, with each group being used as the validation cohort once and as part of the derivation cohort seven times.

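### The only calibration check named for the risk model is a per-fold Hosmer-Lemeshow test, which gives neither size nor direction of error and whose result depends on fold size

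*Protocol article*

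**What the plan says.** The aim 1 population is described as "comprising all women in the cohort who have been identified as having GDM, will be randomly divided into roughly equal subgroups". The study design section gives its expected size: "approximately 475 000 pregnancies, with >70 000 diagnosed with GDM". The number of folds is not fixed. The text illustrates the method "using an 8-fold as an exemplar of the methodology", in which "the whole population gets randomly assigned to eight roughly equal groups" and "these analyses are run eight times, with each group being used as the validation cohort once".

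Performance in the validation cohort is covered in the text after Figure 3. On calibration it says: "agreement between the predicted and observed probabilities of the primary composite outcome will be assessed by Hosmer-Lemeshow goodness of fit testing". Discrimination "will be assessed using area under the receiver operating characteristics curve", and sensitivity, specificity and the two predictive values are computed for each validation cohort. The article names no calibration intercept, slope, curve or observed/expected ratio. It gives no significance level, number of risk groups or degrees of freedom for the test, and no way of combining results over folds.

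The dissemination section says that outputs may include risk prediction tools for use by clinicians in consultations.

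**The concern.** AUC, sensitivity, specificity and predictive values do not compare predicted with observed risk, so the Hosmer-Lemeshow test carries the whole calibration assessment. It has four weaknesses here.

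- Its p-value reports neither the size nor the direction of miscalibration, nor the risk groups in which it lies.
- For a fixed error, the chance of rejection rises with the number of records, so the result partly reflects the choice of k.
- It is repeated in each fold with no stated joint reading, and the folds can disagree about one and the same modelling procedure.
- The usual reference distribution assumes independent records. The article allows for repeat pregnancies in the regression but does not mention them for this test.

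At stake is whether the reported validation can tell a user how far to trust a predicted risk. A non-significant result would not show that the risks are accurate, and a significant one would not show that they are materially wrong.

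**Working it through.** The article gives no power or error-rate figure for this test, so there is no stated figure to reproduce.

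**Inputs from the article.** More than 70 000 GDM pregnancies; k = 8 as an illustration only.

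**Assumptions not in the article.** Alpha 0.05; ten equal risk groups; 10 degrees of freedom (held-out data); event rate 20% or 30%; AUC 0.65 or 0.70; normally distributed linear predictor; mean predicted risk correct; independent records.

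**Step 1: fold size.** 70 000 / 8 = 8 750 pregnancies. For k = 5 it is 14 000, and for k = 10 it is 7 000.

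**Step 2: a perfectly calibrated model.** P(at least one of k folds rejects) = 1 - 0.95^k.

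- k = 5: 22.6%
- k = 8: 33.7%
- k = 10: 40.1%

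This treats folds as independent. A simulated eight-fold cross-validation (70 000 records, 20 predictors, correctly specified, event rate about 20%, 120 runs) gave 37.5%, with 5.8% rejection per fold. If the 8 degrees of freedom meant for development data were used instead, the figures would be 67.5% and 12.6%.

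**Step 3: a model with calibration slope 0.90.** Let e and o be the mean predicted and mean true risk in a decile. The noncentrality is the sum over deciles of (n/10)(o - e)²/(e(1 - e)). The rejection probability is the upper tail of a noncentral chi-square (10 df) beyond the central 95% point.

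| Event rate | AUC | Largest decile error (points) | Rejected, n = 1 000 | Rejected, n = 8 750 |
|---|---|---|---|---|
| 20% | 0.65 | 2.1 | 6.5% | 23.6% |
| 20% | 0.70 | 2.8 | 7.7% | 40.4% |
| 30% | 0.65 | 2.4 | 7.0% | 30.5% |
| 30% | 0.70 | 2.9 | 8.5% | 51.6% |

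The largest error is in the top risk decile in every row. A separate simulation (linear-predictor SD 0.7, 500 runs per setting) agrees. At n = 8 750 it rejects slope 0.90 in 32% (event rate 20%) and 41% (event rate 30%), against about 7% at n = 1 000.

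**Step 4: disagreement between folds.** With per-fold rejection probability p, the chance that eight folds do not all agree is 1 - p^8 - (1 - p)^8.

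- p = 0.236: 1 - 0.000 - 0.116 = 88%
- p = 0.516: 1 - 0.005 - 0.003 = 99%

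**Step 5: a much smaller error.** With slope 0.98 (largest decile error about 0.4-0.5 points) the same formula gives rejection in 5.4-5.9% of folds of 8 750, close to the nominal 5%.

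**The case against.** A reader might infer that folds of this size make the test reject trivial miscalibration almost automatically, so that a sound model would be declared a failure. The article does not support that. At slope 0.90 a single fold does not reject in most of the settings above, and at slope 0.98 the rejection rate is about nominal. Nothing shows that this design would produce a slope of 0.90: each derivation set would hold about 61 250 pregnancies (70 000 - 8 750), so overfitting alone should be slight. An error of 2-3 points in the top decile is also not clearly trivial. The article states no alpha, no pass/fail verdict and no rule that one rejecting fold condemns the model, and it plans no test on all 70 000 pregnancies together.

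Other points also have force. Eight folds is only an illustration. Models that need pathology or clinical maternity data may have smaller folds and less power. The test is built from observed and expected counts by risk group, which would show size and direction if tabulated, and the article does not say that only the p-value will be reported. A calibration plot may stand in a fuller plan that is not shown.

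These points limit the size of the problem but do not remove it. Testing is the stated means of assessing agreement, so this is a choice of method and not merely a detail left out. The predictive values do not fill the gap: a positive predictive value is an observed event rate among those classed as high risk, and it is not set against the predicted risk. Smaller folds would make the test more likely to miss real error, which again shows its dependence on sample size.

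**Conclusion.** The point holds as a weakness in the chosen calibration measure and should be corrected before the model informs any clinical tool. That the p-value lacks size and direction, depends on fold size and has no joint reading over folds needs no numerical assumption. The figures do. Under alpha 0.05, ten groups, event rate 20-30%, AUC 0.65-0.70 and eight folds, slope 0.90 is rejected in about 24-52% of folds, against about 7-9% at 1 000 pregnancies. A perfectly calibrated model shows at least one rejecting fold about 34% of the time (23-40% for k from 5 to 10). These figures show how inconsistent the fold results could be. They do not predict that the model will be rejected, and they do not call the data or the modelling approach into question.

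**What to change.** Replace the Hosmer-Lemeshow test as the calibration measure. Pool the out-of-fold predictions, so that each pregnancy is predicted once by a model that did not use its fold. From these report:

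- the calibration intercept and calibration slope with 95% CIs;
- a smoothed calibration curve with a 95% confidence band;
- observed/expected ratios in the highest and lowest risk groups.

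The intervals should allow for repeat pregnancies to the same woman, for example with woman-level clustered standard errors or a bootstrap that resamples women.

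The cross-validation already generates the predictions, so the cost is a little analysis code and one sentence in the plan. Validation that holds out whole health districts would need the model to be refitted and answers a different question, so it is not part of this change.

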### Analysis plan: gestational age-specific risk associated with planned birth (aim 2)

In order to provide guidance to clinicians on the optimal timing of birth for women with GDM, we will take a ‘target trial emulation’ approach.^27^ The gestational age-specific risk of neonatal morbidity and perinatal mortality will be assessed for planned birth at 37*–*41 weeks’ gestation inclusive. At each gestational week of interest, pregnancies with planned delivery will be compared with pregnancies with expectant management using multivariable logistic regression. Inverse probability weighting will be used to create exchangeability between the delivered and expectantly managed groups (figure 4). The study population for this research question will be restricted to women with diet-controlled GDM with a singleton pregnancy and cephalic presentation. Women with pre-existing comorbidity will also be excluded.

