The NSW Emergency Department Data Collection (EDDC) collates patient presentations to the emergency departments (EDs) of public hospitals and in-scope contracted private hospitals in NSW, including presentations to 184 hospitals in NSW from 2016 to 2017. It includes data on patient demographics, triage category and diagnosis coded to ICD or Systemized Nomenclature of Medicine, Clinical Terms. All ED presentations from January 2005 to December 2021 will be linked with the cohort mothers, and ED presentations from January 2016 to December 2021 will be linked with the cohort babies to provide information on presentations, conditions and health service usage.

The NSW Pathology Data contains pathology test results from NSW public pathology facilities. Relevant pathology test results for the cohort mothers and babies from January 2016 to December 2020 will be linked to the cohort to get more information detail on OGTT results for the mother and blood glucose results for the mother and baby after the birth.

The eMaternity/ObstetriX data system (clinical maternity data) holds information about pregnancy and births in public hospitals in 13 out of 15 NSW local health districts (LHDs). During the study period, these LHDs transitioned from ObstetriX to eMaternity. There was a 6-month system overlap in each LHD, but all were using eMaternity alone by the end of 2017. A minimum dataset from eMaternity/ObstetriX is sent to NSW Health, collated into the PDC, along with the same information from private hospitals, the remaining public hospitals and some independent midwives. The clinical maternity data will be linked with the cohort for a small number of additional variables not in the PDC, but important for the understanding of variation in risk, diagnosis, severity and management of GDM, such as family history of diabetes and type of diabetes therapy during pregnancy. This more detailed maternity data will be linked with the population-level data from January 2016 to December 2020. The estimated NSW birth population coverage linked with each of the additional datasets is shown in figure 2.

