### Defining gestational and pre-existing diabetes

The population with and without diabetes will be defined from the PDC and APDC. From 2016, the PDC revised diabetes capture, distinguishing pre-existing type 1 and type 2 and GDM. The APDC captures diabetes type in the antenatal period (if admitted) or in the birth record. Lookback information for the PDC and APDC will be used to identify women recorded as having GDM, but with pre-existing diabetes recorded in hospital or previous birth records. A previous validation study examining the reporting of diabetes in pregnancy in the PDC and APDC found better recording in hospital data, and as such, both linked datasets will be used to define the diabetes and diabetes type.^24^ Degree of glucose tolerance will be defined using OGTT results from Pathology and clinical maternity data. Whether the diabetes was diet or medication-controlled is recorded in the clinical maternity data.

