### Analysis plan: hospital variation (aim 3)

The hospital variation analyses will examine outcomes for mothers within hospitals. Multilevel modelling takes the hierarchical structure of patients within hospitals into account, quantifying the degree that outcome variation is due to patient characteristics or hospitals.

To make meaningful comparisons between hospitals, an adjustment for different levels of risk in pregnant women in each hospital will be made, using information from the routine datasets (eg, maternal and pregnancy characteristics). Then, unexplained hospital variation in obstetric management and outcomes of pregnancies with GDM will be identified and quantified with the variance partitioning coefficient and, for logistic regression models, the median OR.^28^ The multilevel analyses with single outcomes will be extended to multivariate multilevel models to test the association between obstetric management practices, such as early planned births, and health outcomes.^29^ To understand causal effects (eg, the causal impact of induction of labour on risk of caesarean section among women with GDM), directed acyclic graphs will be used, thereby avoiding over-adjustment and collider bias.^30^ These analyses will also be undertaken within a ‘target trial’ framework, where the exchangeability of treatment groups is emulated through adjustment, eligibility criteria match the hypothetical trial and eligibility criteria are met at or before time zero.^31^

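### Aim 2 compares arms week by week from 37 to 41 weeks, but sets diet-controlled and cephalic status once, with no time anchor, so later starters of medication can drop out of the expectant arm only

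*Protocol article*

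**What the plan says.** The aim 2 analysis section adopts target trial emulation for planned birth at 37 to 41 weeks and repeats the comparison: "At each gestational week of interest, pregnancies with planned delivery will be compared with pregnancies with expectant management using multivariable logistic regression". Each week is therefore its own time zero. Eligibility, by contrast, is given once for the whole research question: "The study population for this research question will be restricted to women with diet-controlled GDM with a singleton pregnancy and cephalic presentation". One further exclusion follows: "Women with pre-existing comorbidity will also be excluded". None of these criteria is tied to a gestational week.

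The section on defining gestational and pre-existing diabetes gives the source of the diet label: "Whether the diabetes was diet or medication-controlled is recorded in the clinical maternity data". The Data sources section describes the field as "type of diabetes therapy during pregnancy". Neither place mentions the date on which treatment started.

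For confounding, aim 2 says: "Inverse probability weighting will be used to create exchangeability between the delivered and expectantly managed groups". The Figure 4 legend also mentions propensity score matching of controls.

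The rule that "eligibility criteria are met at or before time zero" appears in the article, but in the aim 3 section, where it describes the target trial framework.

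**The concern.** In a sequence of weekly emulated trials, a woman's eligibility for week w must depend only on what was known when week w began. Diet-only status can change afterwards, and it can be seen to change only while the pregnancy continues. If the label reflects therapy up to birth, a woman delivered in week w has no further chance to be reclassified, whereas an expectantly managed woman has the rest of her pregnancy in which medication may be started. The restriction then removes women from one arm only, using information from after time zero.

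If the women removed have worse outcomes, the expectant arm is left with a favourable selection. Weights or matching built on the remaining women cannot correct this, because the lost women are no longer in the analysis set. The time left to start medication shortens from week 37 to week 41, so the distortion would probably differ by week and could alter the gestational-age pattern that aim 2 is meant to describe. That pattern is intended to guide clinicians on birth timing.

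Presentation has the same missing anchor. No direction or size of bias is claimed for it here.

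**Working it through.** **No figure to reproduce.** The article gives no event rate, effect size or sample size for aim 2. The first step is therefore a reading of the text, and the next two are illustrations with assumed inputs.

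**Step 1: one woman, two paths.** She is on diet alone at the start of week 37.
- Planned birth in week 37: therapy during the pregnancy was diet only, so she is eligible and counted in the planned arm.
- Expectant management, with medication started at 39 weeks: therapy during the pregnancy includes medication, so a single restriction on that field drops her.

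Her state at time zero is the same on both paths. Only later events decide whether she is counted.

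**Step 2: size of the bias.** Assumed inputs, not from the documents:
- f, the share of women on diet at week w who would later start medication if managed expectantly: 3-10%.
- R, their risk of the outcome relative to the other women: 1.5-2.

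Let r be the risk in women who never start medication. The true expectant risk is r × [(1 − f) + fR]. After later starters are dropped, the observed risk is r. So:

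relative understatement = 1 − 1/[(1 − f) + fR]

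- f = 0.03, R = 1.5: bracket = 0.97 + 0.045 = 1.015; understatement = 1 − 1/1.015 = 1.5%.
- f = 0.05, R = 2: bracket = 0.95 + 0.10 = 1.05; understatement = 1 − 1/1.05 = 4.8%.
- f = 0.10, R = 2: bracket = 0.90 + 0.20 = 1.10; understatement = 1 − 1/1.10 = 9.1%.
- R = 1, any f: bracket = 1; no bias.

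If timing of birth truly had no effect, the bracket is also the spurious planned-versus-expectant risk ratio: 1.015, 1.05 and 1.10 in the first three cases. A wider range (f = 1-10%, R = 1.5-3) gives 1.005 to 1.20. With eligibility judged at the start of each week, nobody is dropped for later treatment and the ratio returns to 1.00.

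**Step 3: conditions acquired in pregnancy.** Only pre-existing comorbidity is excluded, so conditions that arise in pregnancy stay in the population. If such a condition has prevalence pP in the planned arm and pE in the expectant arm, carries risk ratio R and is left wholly unadjusted, the spurious ratio is [1 + pP(R − 1)]/[1 + pE(R − 1)].
- pP = 0.20, pE = 0.10, R = 1.5: 1.10/1.05 = 1.05.
- pP = 0.40, pE = 0.10, R = 3: 1.80/1.20 = 1.50.

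These inputs are also assumed. If the condition is measured before week w and is in the weights, the ratio is 1.00. The Explanatory variables section lists gestational hypertension, pre-eclampsia, and growth restriction and macrosomia identified antenatally, so the planned method can use them. The open matter is timing: a condition that arises after week w in an expectant woman is a possible consequence of waiting and should not enter the weights as a baseline confounder.

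**The case against.** The strongest reply is that the text leaves the time point unspecified rather than fixing a wrong one. Nothing in the article expressly says that diet control is judged over the whole pregnancy, and the description of the therapy field is an example of a linked variable, not the eligibility definition. Aim 2 invokes target trial emulation. The aim 3 wording says that its analyses are also done in that framework, so the time-zero rule may be meant for both aims. The aim 2 flowchart is not visible here, and a journal article leaves detail to fuller documents.

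Much of this stands. The bias is conditional on how the label is applied, and the article should not be said to have broken its own rule. What does not fall away is that the article states one restriction for an analysis repeated over five weeks, draws it from a field described per pregnancy, and writes the protective rule only under another aim. An analyst who followed the text literally would introduce the selection.

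A reader might also infer that acquired complications sit almost wholly in the planned arm, that they must be excluded, or that they force inverse probability weights of 10-20. The documents support none of these. The conditions can occur in both arms, and several are listed covariates available to the weighting. Weights of that size need an assumed 90-95% chance of delivery in the week, through 1/(1 − 0.90) = 10 and 1/(1 − 0.95) = 20, and the article gives no such figure.

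**Conclusion.** The point holds as a conditional selection problem. Followed as written, the aim 2 restriction can remove women who start medication after week w from the expectant arm alone, and the planned weighting or matching cannot repair that. Under assumed escalation of 3-10% and 1.5-2 times the risk, the understatement of expectant risk is about 1.5-9% in relative terms. It is nil if later starters have no excess risk, and probably smaller at later weeks. Neither the escalation share nor the excess risk is in the documents, so the direction rests on the assumption that women who go on to medication do worse. For acquired conditions, what remains is a request to state how they are handled and at what time they are measured. Because the comparison is meant to guide birth timing and the repair is cheap, the change should be made.

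**What to change.** Carry the aim 3 time-zero rule into the aim 2 text:

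- For each week w from 37 to 41, judge eligibility at the start of the week from information recorded by then: undelivered, on diet alone to date, last recorded presentation cephalic.
- Keep women who start medication after that point in the arm they were in.
- Build the weights or matching only on covariates recorded before week w, including the listed conditions acquired in pregnancy, such as pre-eclampsia.
- State which acquired conditions are handled by eligibility and which by weighting, with the same rule for both arms. That choice belongs to the investigators.
- If the start of therapy is undated, report a sensitivity analysis that returns medication-treated women who have no earlier record of treatment.

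The cost is a few sentences of wording, date logic for each week and possibly one sensitivity analysis. No new data collection is proposed. The main limit is that undated fields would leave some uncertainty, which the sensitivity analysis would show but not remove.
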